## Abstract

**Background:**

Cardiovascular disease is the leading cause of disability and mortality in most Western countries. The prevalence of several risk factors, most notably low physical activity and poor nutrition, is very high. Therefore, lifestyle behaviour changes are of great importance. The worksite offers an efficient structure to reach large groups and to make use of a natural social network. This study investigates a worksite health promotion programme with individually tailored advice in physical activity and nutrition and individual counselling to increase compliance with lifestyle recommendations and sustainability of a healthy lifestyle.

**Methods/Design:**

The study is a pragmatic cluster randomised controlled trial with the worksite as the unit of randomisation. All workers will receive a standard worksite health promotion program. Additionally, the intervention group will receive access to an individual Health Portal consisting of four critical features: a computer-tailored advice, a monitoring function, a personal coach, and opportunities to contact professionals at request. Participants are employees working for companies in the Netherlands, being literate enough to read and understand simple Internet-based messages in the Dutch language.

A questionnaire to assess primary outcomes (compliance with national recommendations on physical activity and on fruit and vegetable intake) will take place at baseline and after 12 and 24 months. This questionnaire also assesses secondary outcomes including fat intake, self-efficacy and self-perceived barriers on physical activity and fruit and vegetable intake. Other secondary outcomes, including a cardiovascular risk profile and physical fitness, will be measured at baseline and after 24 months.

Apart from the effect evaluation, a process evaluation will be carried out to gain insight into participation and adherence to the worksite health promotion programme. A cost-effectiveness analysis and sensitivity analysis will be carried out as well.

**Discussion:**

The unique combination of features makes the individually tailored worksite health promotion programme a promising tool for health promotion. It is hypothesized that the Health Portal's features will counteract loss to follow-up, and will increase compliance with the lifestyle recommendations and sustainability of a healthy lifestyle.

**Trial registration:**

Current Controlled Trials ISRCTN52854353.

## Background

### Cardiovascular disease

Cardiovascular disease (CVD) is the leading cause of disability and mortality in most Western countries. CVD causes nearly half of all deaths in Europe (49%) [1]. Major modifiable risk factors for CVD include smoking, alcohol use, low physical activity (PA), and poor nutrition. The prevalence of several risk factors is very high, most notably low PA and poor nutrition (low fruit and vegetable consumption and high saturated fat intake).

According to a survey in European Union countries in 2002, 56% of the Dutch population over 15 years was insufficiently physically active for health [2]. The Dutch recommendation on PA stipulates that an adult should engage in PA of at least moderate intensity for at least 30 minutes a day on five days a week, and preferably every day in order to obtain health benefits [3]. In 2006, about half of the Dutch adults (25–55 year) met this recommendation [4]. In order to improve physical fitness it is recommended to engage in PA of vigorous intensity for at least 20 minutes on at least three days a week [3]. Exercise capacity has been found to be a powerful predictor of mortality [5]. It has been estimated that the life expectancy for people with low PA levels at age over 50 is 1.4 years less than for people with moderate PA levels and even 3.8 years less than for people with high PA levels [6].

The results of a recent meta-analysis on cohort studies indicate that fruit and vegetable consumption is inversely associated with the occurrence of coronary heart disease. The risk of coronary heart disease decreased by 4% for each additional portion of fruit and vegetables per day [7]. In the last representative Dutch food intake survey in 1997/1998 less than a fourth of the Dutch population met the recommendation for vegetable (200 grams a day) and fruit intake (200 grams a day) [8]. Regarding saturated fat intake, only 9% of the Dutch adult population met the recommendation (a maximum of 10 percent of energy intake as saturated fat) in 1997/1998 [9]. A high intake of saturated fat increases the risk of coronary heart disease [10].

The imbalance between PA and nutrition is an important cause of overweight and obesity, which in turn are important risk factors for CVD [11]. In the Netherlands self-reported overweight (body mass index ≥ 25) in adult men increased from 37% in 1981 to 51% in 2004, and in adult women from 30% in 1981 to 42% in 2004 [12].

### Worksite health promotion

In the prevention of cardiovascular disease, lifestyle behaviour changes are of great importance. Worksites have specific features that make them a promising place for health promotion. Worksites offer an efficient structure to reach large groups, enable the introduction of social support, and make use of a natural social network for peer support [13,14].

Literature shows contradictory results of randomised controlled trials (RCTs) on worksite health promotion programmes (WHPPs). A recent systematic review concluded that there is strong evidence for effectiveness of WHPP, based on two RCTs with a small effect on exercise behaviour and on energy expenditure [15]. However, another review on worksite PA programmes reported a small average effect size of 0.04 (95% CI -0.04–0.12) based on RCTs on self-reported level of PA 1–144 months after the intervention ceased [13]. A third review on environmental and policy interventions presented preliminary evidence that combined health education, screening, counselling, peer support, and access to (on-site) exercise equipment had positive effects on fitness levels, frequency of exercise, cholesterol levels, and systolic blood pressure. Several randomised studies on point-of-purchase nutrition interventions, some in worksites, showed positive effects on fruit and vegetable consumption, self-reported fat intake, cholesterol, and body weight but other studies have failed to corroborate these findings [16].

The overall picture emerges that WHPP may increase PA and improve nutritional intake among targeted groups, depending on the critical features of the interventions. Amongst others, as success factors of WHPP have been identified: (1) interventions tailored to the individuals' readiness for exercise adoption, (2) programmes that integrate specific components (nutrition, smoking, PA) into a combined approach, and (3) linking individual approaches to environment and policy conditions [17]. Marcus and colleagues showed that workers receiving self-help exercise promotion material tailored to the individual's readiness were significantly more likely to have increased exercise [18]. An individualized approach of high risk employees within the framework of a comprehensive program proved to be a critical feature of worksite interventions [19]. Recent studies have shown that web-based education tailored to personal characteristics may increase fruit and vegetable consumption and PA level, and decrease fat intake. In these interventions people received personalized feedback and advice that directly matched their individual behaviour, motivation, perceived (dis)advantages, and self-efficacy beliefs [20]. Based on results of their study on email messages to promote health behaviours, Franklin et al. suggest that emails may contribute tot the effective deliverance of health promotion programmes [21].

In contrast, three factors have been identified as greatest risks for ineffective WHPP: (1) a low, selective participation, (2) lack of adherence to the WHPP, and (3) an intervention effort too short for sustainable change in behaviour [13,15,16]. In several worksite studies intervention and evaluation periods were too short to determine the sustainable impact of environmental conditions [16].

In conclusion, previous WHPPs have shown contradictory results. Studies are needed on a WHPP that counteracts the three main factors for ineffectiveness.

In the study protocol described in this article, a long-term WHPP will be evaluated that adds the following four critical features to a traditional WHPP: (1) a computer-tailored advice on PA and diet (to increase awareness and adherence to the WHPP) (2) insight in progress over time on health-related behaviours (to increase adherence to the WHPP, compliance with the lifestyle recommendations and sustainability of a healthy lifestyle), (3) continuous feedback and support through monthly e-mails (personal coach) for 12 months (to increase adherence to the WHPP and compliance with and sustainability to the lifestyle recommendations), and (4) opportunities to seek personal advice from a variety of professionals (to increase adherence to the WHPP).

### Objectives

The aim of this pragmatic cluster randomised controlled trial is to evaluate the cost-effectiveness of a new investigator-driven WHPP with individually tailored advice in PA and nutrition and individual counselling to increase compliance with the lifestyle recommendations and sustainability of a healthy lifestyle.

## Methods/Design

### Study design and population

The study is a single blind pragmatic cluster randomised controlled trial with the worksite as the unit of randomisation. The (evaluation of the) intervention is targeted at the individual level. The study population consists of workers in companies that offer a standard WHPP to their employees, as provided by an organisation specialized in health management (LifeGuard Inc., Utrecht). Eligibility criteria for individual workers in the study are: 1) paid employment, 2) working at least 12 hours a week, and 3) being literate enough to read and understand simple e-mail and Internet-based messages in the Dutch language. All participants are blinded to the type of intervention. Data collection starts in September 2007 and will continue until August 2010. Participants will be requested to fill out a questionnaire at baseline and after 12 and 24 months. A physical examination (the 'health check') will take place at baseline and after 24 months. The study design and participant flow are shown in Figure 1. The Medical Ethics Committee of Erasmus MC, University Medical Center Rotterdam, the Netherlands, has approved the study protocol.

**Figure 1 F1:**
[figure not shown]
Flow of participants through the trial.

### Randomisation

Within each company, units will be randomised by a researcher not involved in the study, based on a table of random numbers (SAS command Ranuni). Within each company, worksites with comparable work activities and a comparable number of workers will be randomly allocated to the intervention or the control group. Subsequently, workers within each unit will be asked to participate in the study, presented as an evaluation study of different types of WHPP. All participants from one worksite will be randomised together rather than individually because individual randomisation may lead to contamination of the control group. Written informed consent at individual level is collected after agreement of the employer and randomisation at cluster level. Since it is deemed not possible within companies to withheld participation in a WHPP, workers within the control group will receive a standard WHPP.

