#### Computer-tailored advice

Participants will receive a computer-tailored advice to increase awareness of their lifestyle [22]. Awareness is found to be an important mediator of participation in health promotion programmes [23]. The benefits of computer tailoring is attributed to the fact that individualized feedback commands greater attention, is processed more intensively, contains less redundant information, and is appreciated better than the provision of general documentation [24].

After baseline measurements the participant in the intervention group will receive an email with the notification that a personal advice is available on the Health Portal. Considering the answers on the questionnaire filled out at baseline a personal advice on PA, fruit and vegetable consumption, and fat intake will be generated. The advice aims to increase adherence to the intervention and to motivate the participant to engage in PA and a healthy diet, and consists of the following parts:

1) Personal feedback: feedback on to what extent the recommendations on PA and dietary intake are met.

2) Action feedback: feedback on the specific barrier attributed by the participant as most important to not meeting the recommendations. The advice also contains opportunities to link to further information on the Health Portal and provides tips on how to meet the guidelines.

If one meets the recommendations, only the personal feedback is provided. See Figure 2 for an example of the computer tailored advice.

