### Sample size

The assumptions for the power calculations were: an intra-cluster correlation of 0.05 (as observed in a previous cluster RCT in companies [39]), an average of 20 workers per cluster, a power of 80%, and a level of significance of 5% (one-sided). Under these assumptions, we anticipate to be able to detect a difference of at least 12% in prevalence between intervention and control group (e.g. primary outcome measure 30% compliance with the recommendation for PA up to 42%) with 350 workers with completed questionnaires assigned to the intervention. Without a noticeable intra-cluster variance the detectable difference will increase by 9%. With an initial participation of 70% and loss-to-follow-up of 30%, the cluster RCT should invite 2*700 workers.

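### Workers are invited and give consent after their worksite is allocated, and blinding is stated only for participants, so who joins can still differ by arm

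*Protocol article*

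**What the plan says.** Under Randomisation, worksites similar in type of work and size are allocated within each company, and "units will be randomised by a researcher not involved in the study". Recruitment comes next: "Subsequently, workers within each unit will be asked to participate in the study, presented as an evaluation study of different types of WHPP". The same section adds: "Written informed consent at individual level is collected after agreement of the employer and randomisation at cluster level".

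Under Study design and population, the article states: "The study is a single blind pragmatic cluster randomised controlled trial with the worksite as the unit of randomisation". It names one blinded party: "All participants are blinded to the type of intervention".

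The Abstract and the Standard program section give the questionnaire, the health check and the advice based on them to both arms. The first contact specific to one arm is described under Computer-tailored advice: "After baseline measurements the participant in the intervention group will receive an email", which announces the tailored advice on the Portal.

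The Sample size section starts its recruitment sum "With an initial participation of 70" per cent, with 30% loss to follow-up and 2 × 700 workers invited. The non-response analysis under Participation lists age, sex, education, job title, company size and the company's history of health promotion. It is not stated to be by arm and does not list baseline activity or diet.

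**The concern.** Randomising worksites makes the worksites comparable. It does not make the workers who agree to take part comparable if their agreement comes after the allocation and can be influenced by it. An employer or recruiter who knows that a unit will get the full Portal may promote the study harder there, or to different people. The arms would then differ at entry in motivation or behaviour, and part of any difference at 12 or 24 months would reflect who joined.

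The primary outcomes are self-reported compliance with activity and with fruit and vegetable recommendations, and readiness to join a health programme is plausibly related to both. The Background itself counts low and selective participation among the main reasons why worksite programmes fail. Adjusting for measured baseline behaviour would reduce such an imbalance. It would not remove a difference in unmeasured motivation to change.

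**Working it through.** **1. Order of events.** Placing the sections side by side gives: employer agrees; worksites are allocated; workers are invited; workers consent; baseline questionnaire and health check; arms diverge. The order is stated, so this point does not rest on an omission.

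**2. Does any step need the allocation earlier?**
- Matching uses type of work and number of workers. Both are worksite features known without individual consent.
- The questionnaire and health check are the same in both arms.
- The tailored advice is generated from the baseline answers, so it cannot precede them.
- The restricted and full versions of the Portal differ, but workers' results can appear there only once they have been measured.
- The contamination argument under Randomisation supports randomising whole worksites. It does not bear on when the allocation is released.

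The allocation is therefore not needed before an individual's baseline is complete. It may be needed soon afterwards, if workers finish baseline at different times.

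**3. Room for selection (the plan's own figures).** Per arm, 700 × 0.70 = 490 participate and 210 decline. With 30% loss, 490 × 0.70 = 343 complete, close to the stated 350.

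**4. Illustrative size.** The documents give no rate of differential participation, so these inputs are assumptions. If a share s of one arm's participants are extra joiners whose compliance is d points above that of the others, the arm's compliance becomes (1 − s)p + s(p + d) = p + s·d. The shift is s × d:

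| Share s | d = 10 points | d = 30 points |
|---|---|---|
| 5% | 0.5 | 1.5 |
| 10% | 1.0 | 3.0 |
| 15% | 1.5 | 4.5 |

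Against the 12-point target (30% to 42%), the range is 0.5/12 = 4% to 4.5/12 = 38%.

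**5. Would the overall participation rate reveal it?** Assume that 30% of invited workers comply in both arms, that control participation is 70% whatever the behaviour, and that the intervention has no effect. If compliers and non-compliers in the intervention arm join at rates a and b, compliance among participants is 0.30a / (0.30a + 0.70b).
- a = 75%, b = 70%: 0.225 / 0.715 = 31.5%, a spurious +1.5 points, with overall participation of 71.5%.
- a = 80%, b = 65%: 0.240 / 0.695 = 34.5%, a spurious +4.5 points, with overall participation of 69.5%.

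The second case sits almost exactly on the planned 70%, so the rate alone would not show the problem. With 350 per arm and a design effect of 1 + 19 × 0.05 = 1.95 (effective size 350 / 1.95 = 179.5), the one-sided 5% error would be about 9% and 23% in these two cases, in an analysis not adjusted for baseline behaviour.

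**The case against.** The case on the other side has substance.

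- **Workers are protected from self-selection to a fair degree.** They are blinded, the study is presented neutrally, and both arms see the same package at entry. The Discussion relies on the health check to raise participation, and the health check is common to both arms. This stands. A worker who does not know the arm has no arm-related reason to join or decline. What remains is influence from people who may know it.
- **The article does not say who recruits.** A reader might infer that the provider's staff invite workers and know the allocation. The document does not support that: the invitation is described without naming who makes it, and the participant-flow figure is not shown. The concern is only that no one other than participants is stated to be unaware.
- **A condensed article may omit concealment procedures.** That is fair, and silence alone would not be a finding. The order of allocation and consent is stated, however, and it is what makes concealment from recruiters necessary.
- **Early allocation may have a use.** A reader might infer that it serves no purpose. That is too strong: if baseline is completed on a rolling basis, the first worker to finish needs an allocation while others are still being invited.
- **The magnitude is assumed, and baseline behaviour is measured.** Both are true. Confounders are also listed, and continuous outcomes use a repeated-measurements model. The figures above are therefore shifts before adjustment.

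**Conclusion.** The point holds as a weakness in a stated design choice. Recruitment and consent follow allocation, blinding is stated for participants only, and no described procedure requires the allocation before an individual's baseline is complete. Participation can therefore differ by arm, and the planned non-response analysis, as described, might not show it.

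The documents do not show that participation will differ or that the comparison is biased, and that should not be inferred. The direction is also open, since an informed recruiter could raise or lower participation in either arm. The range of 0.5 to 4.5 points rests entirely on the assumed 5% to 15% extra joiners and 10 to 30 points higher compliance. It shows that modest selection would matter against a 12-point target; it does not estimate what will happen. The change is worth making because it costs little and the risk cannot be fully repaired in the analysis.

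**What to change.** Within each company, complete invitation, consent, baseline questionnaire and health check in the matched worksites first. The independent researcher then releases the allocation.

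Where logistics or rolling baseline prevent this, withhold the allocation from employer contacts and from whoever invites and measures workers until that worksite's baseline is complete. State in the protocol who is kept unaware and until when.

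In both cases, compare participation and baseline compliance with the activity, fruit and vegetable recommendations by arm. Non-participants' behaviour is not described as recorded, so comparing participants' baseline compliance between arms is the practical check.

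**Cost.** Sample size and measurements do not change. Early participants wait for Portal activation until the baseline round closes, so their advice rests on somewhat older answers. The wait must fit the timetable: September 2007 to August 2010 is 36 months, and 24 months of follow-up leave roughly 12 for enrolment. Closing the round company by company keeps the delay short.

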### Standard program

The standard WHPP consists of:

1) A questionnaire to assess, among other things, PA level and fruit and vegetable intake.

2) A health check to assess weight, length, total blood cholesterol level, blood pressure, resting heart rate, body mass index (BMI), percentage of body fat, and predicted maximal oxygen uptake.

3) Advice of the provider's personnel, based on the outcomes of the questionnaire and health check. In addition, workers with a high total cholesterol level or high blood pressure will be referred to their general practitioner.

4) Access to a restricted part of the Health Portal on Internet, containing general information on health and health-related behaviours. The individual results on the questionnaire and health check are also retrievable through this web site.

### Intervention

On top of the standard WHPP the intervention group will have full access to the personalized Health Portal on Internet. The Portal contains four critical features: a computer-tailored advice, a monitoring function, a personal coach, and opportunities to contact professionals at request.

